**5. Study regimen**

### 5.1 Study steps and procedures

1. The screening procedure begins after the patients sign the written informed consent.
2. CT and/or MRI scans (with PET-CT where available) are used to assess liver metastases and to exclude extrahepatic metastases.
3. An MDT meeting is held prior to chemotherapy and the resectability of metastases is assessed and determined based on the given criteria. The liver surgeon performs a comprehensive assessment of each patient’s baseline liver metastases, record in detail the number and size of liver metastases, the liver segment involved, whether the hepatic vein, portal vein, and inferior vena cava are involved, and explain in detail why each patient is considered initially unresectable.
4. Eligible patients at screening are randomly assigned by the study physician to receive either cetuximab plus FOLFOXIRI triplet regimen or cetuximab plus FOLFOX doublet regimen.
5. CT and/or MRI scans are performed every 4 cycles after chemotherapy, with additional examinations if necessary, and the tumor is assessed according to RECIST v1.1 criteria; MDT discussion is held regularly to determine the resectability of patients’ liver metastases. The reason why each patient can be converted to surgically resectable is also specified.
6. In this study, 8 courses (no less than 6 courses) of conversion chemotherapy are recommended, and some patients also need to appropriately prolong the treatment course. This is mainly because that this study includes patients with unresectable colorectal liver metastases, who usually have a large number of liver metastases, large lesions, with high-risk CRS score. Current clinical practice recommends surgical resection after adequate chemotherapy to achieve more benefit.
7. For the treatment of liver metastases, surgical resection with or without intraoperative radiofrequency treatment can be used. For the lesions that cannot be resected or treated with radiofrequency during surgery but are suitable for SBRT treatment, SBRT should be added after surgery. The timing of resection of primary intestinal lesions can be determined by the investigator according to the patient’s condition. For patients with liver metastases converted to surgical resectable, primary intestinal disease can be resected before chemotherapy, or can be resected at the same time or in stages with liver metastases after successful conversion. For patients with rectal cancer, local rectal radiotherapy can be performed when needed, and long-course or short-course radiotherapy can be used.
8. Patients with liver metastases can receive chemotherapy alone with or without cetuximab as adjuvant chemotherapy after surgery. Patients in the cetuximab + mFOLFOXIRI regimen group can receive doublet regimen chemotherapy after surgery. Patients should receive tumor assessment before postoperative adjuvant chemotherapy, including at least CEA, liver MRI scan + enhanced scan, and chest and lower abdomen pelvic CT (if necessary). Patients will receive up to a total of 12 courses of chemotherapy before and after surgery, and treatment will be interrupted in the event of disease progression, intolerable adverse reactions, or patient refusal.
9. For patients who cannot undergo surgery or are unwilling to receive surgery but can receive radiofrequency treatment, radiofrequency treatment can be given. The total number of planned chemotherapy courses treated before and after radiofrequency treatment is 12 courses.
10. For patients who received adequate chemotherapy and whose tumor is controlled (PR or SD achieved) but still cannot undergo resection or radiofrequency, the treatment regimen can be changed for conversion therapy, and once the conversion is successful, surgical treatment and/or radiofrequency therapy can be performed. These patients may also discontinue chemotherapy or enter maintenance chemotherapy.
11. Patients who have disease progression during chemotherapy can discuss with investigator to decide whether to receive further palliative treatment. For patients with unresectable liver metastases after chemotherapy, whether to perform the primary lesion resection can be decided according to the patient’s wishes and specific circumstances.
12. Patients who have completed the treatment specified in the protocol or have not completed the treatment due to intolerable toxicity, but have not experienced tumor progression, are followed up every 3 months, including physical examination and imaging examination until tumor progression. For patients with tumor progression, follow-up will be performed by phone every 3 months until death. The following information should be collected as much as possible during follow-up: subsequent anti-tumor treatment and survival data. Patients with preoperative disease progression should withdraw from the study and enter the follow-up period as well.

Flowchart:

Technically resectable but ≥ 5 metastatic lesions or technically unresectable

Randomization

Cetuximab plus FOLFOXIRI

Cetuximab plus FOLFOX

Chemotherapy: 6 to 8 courses (3 to 4 months)

Resectable

Progression

Disease controlled but remains unresectable

Switch to other therapy or maintenance therapy

Surgical resection

Continue chemotherapy: 4 to 8 courses (2 to 3 months)

Switch to other therapy

Progression

### 5.2 Dosing regimens and treatment courses

**Preoperative conversion chemotherapy regimen:**

Eligible patients enrolled are randomized to receive either triplet regimen of cetuximab plus FOLFOXIRI or doublet regimen of cetuximab plus FOLFOX. The specific regimen is as follows:

**Cetuximab + mFOLFOX6 regimen**

Cetuximab 500 mg/m^2^ ivd 90 min d1

Oxaliplatin 85 mg/m^2^ ivd 3h d1

L-leucovorin 200 mg/m^2^ ivd 2h d1 (d,l-leucovorin 400 mg/m^2^)

5-FU 400 mg/m^2^ iv d1

5-FU 2400 mg/m^2^ ivd civ 46h d1

**Cetuximab + mFOLFOXIRI regimen**

Cetuximab 500 mg/m^2^ ivd 90 min d1

Irinotecan 130 mg/m2 ivd d1 (The starting dose of irinotecan is 130 mg/m2, according to the “3 + 3” design. If 0/3 patients experience dose limiting toxicity (DLT), the dose should be increased to 150 mg/m2; if 1/3 patients experiences DLT, the number of enrolled patients should be increased to 6; if ≤ 1/6 patients experience DLT, the dose should be increased to 150 mg/m2; if ≥ 2/6 patients experience DLT, the dose of irinotecan should be decreased to 100 mg/m2.

At the dose of 150 mg/m2, if 0/3 patients experience DLT, the dose is determined to be 150 mg/m2; if 1/3 patients experiences DLT, the number of enrolled patients should be increased to 6; if ≤ 1/6 patients experience DLT, the dose is determined to be 150 mg/m2; and if ≥ 2/6 experience DLT, the dose is determined to be 130 mg/m2). UGT gene detection is recommended. For patients with UGT*28 7/7, UGT*6 A/A, UGT*28 6/7 and UGT*6 A/G, irinotecan at the dose of 130 mg/m2 is used, no need for escalation)

Oxaliplatin 85 mg/m^2^ ivd 3h d1

L-leucovorin 200 mg/m^2^ ivd d1 (d,l-leucovorin 400 mg/m^2^)

5-FU 2400 mg/m^2^ ivd civ 46h d1

The above regimen is repeated every 14 days.

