**6.2 Dose modifications due to hematologic toxicity**

Dose modifications during this or subsequent cycles due to DLT are made as follows:

- For Grade 3 ANC decreased, dose modification of investigational drugs (oxaliplatin/irinotecan, 5-FU) is not needed. For Grade 3 PLT decreased, febrile Grade 3 ANC decreased, or Grade 4 ANC decreased, adjust the dose of oxaliplatin/irinotecan to 80% of the original dose. For Grade 4 PLT decreased or febrile Grade 4 ANC decreased, adjust the dose of oxaliplatin/irinotecan to 70% of the original dose.
- After a dose reduction, if the same or higher grade of toxicity recurs, further reduce the dose of oxaliplatin/irinotecan to 60%. If Grade 4 toxicity persists despite dose modification for Grade 4 toxicity, discontinue oxaliplatin/irinotecan and continue the treatment with cetuximab or FU/CF chemotherapy.
- After the second dose reduction, if the same or higher grade of toxicity recurs, discontinue oxaliplatin/irinotecan and continue the treatment with cetuximab or FU/CF chemotherapy.

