**6.3 Dose modifications due to non-hematologic toxicity**

If the non-hematological toxicity is not clearly related to a certain investigational drug, consider adjusting the dose of all drugs that may cause the adverse reactions; if the non-hematological toxicity is clearly related to a certain investigational drug, consider only adjusting the dose of this drug, while the dose of other investigational drugs may not be adjusted.

Dose adjustment for the first occurrence of non-hematological toxicity:

- Diarrhea
- If diarrhea occurs at any time, the patient must recover to less than Grade 1 diarrhea before restarting treatment. For Grade 1 diarrhea, administer the investigational drug at the original dose; for Grade 2 diarrhea, administer irinotecan and 5-FU at 85% of the original dose; after a dose reduction, if the same or higher grade of toxicity recurs, further reduce irinotecan and 5-FU to 75% of the original dose. For Grade 3 diarrhea, administer irinotecan and 5-FU at 75% of the original dose; after dose reduction, if the same or higher grade of toxicity recurs, further reduce irinotecan and 5-FU to 60% of the original dose. If the patient presents with the following conditions, including Grade 4 diarrhea, diarrhea with fever, and diarrhea with Grade 3 to 4 granulocytopenia, administer irinotecan and 5-FU at 60% of the original dose. After dose reduction, discontinue the treatment if the same or higher grade of toxicity recurs.
- Bilirubin increased

Once bilirubin increased occurs, it is recommended to rule out bilirubin increased caused by biliary obstruction and tumor progression. If bilirubin is > 1.5 × ULN, irinotecan is no longer recommended.

- Transaminases increased

In this study, if the transaminases level is abnormal, it is recommended to rule out transaminase increased caused by tumor progression. Drug treatment will be withheld until toxicity recovers to baseline or ≤ Grade 1 before treatment can be restarted. For Grade 1 and 2 transaminases increased, no dose adjustment is made; for Grade 3 transaminase increased, adjust the dose of oxaliplatin/irinotecan to 80% of the original dose. For Grade 4 transaminases increased, discontinue all treatment. Once a dose reduction has been made due to hepatic function, no further dose reduction is recommended if no worsening of indicators is observed.

- Stomatitis

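### If irinotecan 130 mg/m2 fails the 3+3 rule and the general dose falls to 100, patients with the listed UGT genotypes are still assigned the rejected 130 mg/m2

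*Protocol*

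**What the plan says.** The rule stands in Protocol section 5.2, under the cetuximab + mFOLFOXIRI regimen. The entry level is fixed first: "The starting dose of irinotecan is 130 mg/m2, according to the “3 + 3” design". With no DLT in three patients, or at most one in six, the dose goes up to 150 mg/m2. Expansion follows the usual pattern: "if 1/3 patients experiences DLT, the number of enrolled patients should be increased to 6". The downward step is "if ≥ 2/6 patients experience DLT, the dose of irinotecan should be decreased to 100 mg/m2". At the higher level, "if ≥ 2/6 experience DLT, the dose is determined to be 130 mg/m2".

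After these rules, and outside the parenthesis that holds them, come two sentences on genotype. The first is "UGT gene detection is recommended". The second names UGT*28 7/7, UGT*6 A/A, UGT*28 6/7 and UGT*6 A/G and states that for these patients "irinotecan at the dose of 130 mg/m2 is used, no need for escalation".

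Nothing else in the protocol links the genotype dose to the outcome of the 3+3 rule. Sections 6.2 to 6.5 adjust an individual patient's dose after toxicity has occurred; they do not set starting doses.

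**The concern.** The genotype sentence states a dose, not a ceiling. It removes the step up to 150 but does not say what happens if the general dose steps down. On that branch the literal instruction gives the genotype group 130 mg/m2 while all other patients in the arm start at 100.

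That reverses the purpose of the clause. No outside knowledge of UGT is needed to see this: the protocol itself marks these patients as the ones not to escalate, yet on one of its own planned branches it treats them at a level that has just failed the trial's toxicity rule. What is at stake is the safety of those patients. The comparison of response rates is not in question.

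**Working it through.** **Branches of the written rule**

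| 3+3 outcome | General dose (mg/m2) | Listed genotypes (mg/m2) | Reading |
|---|---|---|---|
| 130 passes, 150 passes | 150 | 130 | consistent cap |
| 130 passes, 150 fails | 130 | 130 | consistent |
| 130 fails | 100 | 130 | conflict |

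On the third branch the ratio is 130/100 = 1.30, that is, 30% more at the rejected level.

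**Do the section 6 reductions close the gap?**

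These are percentages of the original dose, read here as the patient's assigned starting dose. From 130 mg/m2, a first reduction gives:

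- 85%: 130 × 0.85 = 110.5 mg/m2. Section 6.3: "for Grade 2 diarrhea, administer irinotecan and 5-FU at 85% of the original dose".
- 80%: 130 × 0.80 = 104 mg/m2. Section 6.2: "Grade 4 ANC decreased, adjust the dose of oxaliplatin/irinotecan to 80% of the original dose".
- 75%: 130 × 0.75 = 97.5 mg/m2 (Grade 3 diarrhoea, section 6.3).
- 70%: 130 × 0.70 = 91 mg/m2 (Grade 4 platelet decrease or febrile Grade 4 neutrophil decrease, section 6.2).
- 60%: 130 × 0.60 = 78 mg/m2 (Grade 4 diarrhoea, or diarrhoea with fever or with Grade 3–4 granulocytopenia, section 6.3).

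After the two milder cuts the patient is still above the 100 mg/m2 at which others start. Only cuts to 75% or lower bring the dose below it. All of them act after toxicity has occurred, so none corrects the starting dose.

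**How likely is the third branch?**

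The protocol gives no DLT rate, so the true rate p at 130 mg/m2 is an assumption, shown over a range. Let X be the number of DLTs in the first three patients.

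- Literal rule (exactly 1 of 3, expand, then at least 2 of 6): P = 3p(1−p)² × [1 − (1−p)³].
- Also counting X ≥ 2 in the first three as failure: add 3p²(1−p) + p³. With two DLTs already seen, at least 2 of 6 is certain.

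| Assumed p | Literal rule | P(X ≥ 2) | Both |
|---|---|---|---|
| 10% | 0.243 × 0.271 = 0.066 | 0.028 | 0.094 |
| 20% | 0.384 × 0.488 = 0.187 | 0.104 | 0.291 |
| 30% | 0.441 × 0.657 = 0.290 | 0.216 | 0.506 |
| 40% | 0.432 × 0.784 = 0.339 | 0.352 | 0.691 |

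These are chances that the trial enters the branch, not chances that a given patient is over-dosed. The latter would also need the genotype frequency and the uptake of testing, and the protocol gives neither.

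**The case against.** The strongest reply is that the clause was never meant to apply on the downward branch. It follows directly after the rules for 150 mg/m2, a stage reached only once 130 has passed, and it closes by exempting these patients from escalation. Read that way, it only says whom not to take to 150. This is probably what the authors had in mind, but the text does not confine the sentence to that stage. It gives a dose without a condition, and an investigator should not have to infer an exception to a dosing instruction.

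Second, several conditions must coincide: 130 fails, the patient is in the triplet arm, was genotyped and carries a listed genotype, and the clause is followed literally. That stands, and it limits the scope. The protocol wrote the downward branch itself, however, so the branch has to work.

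Third, the probabilities rest wholly on assumed DLT rates. Of the irinotecan doses the Background quotes for earlier cetuximab-triplet studies (130, 150 and 180 mg/m2), 130 is the lowest. That stands too: nothing in the document favours the high end of the range, and the table should be read as a range only. The literal-rule column is the less natural reading of a 3+3 design, under which two DLTs in three patients would normally end the level.

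Fourth, section 6 has further safeguards: the cut to 60%, a recommendation against irinotecan once bilirubin exceeds 1.5 × ULN, and recovery criteria before each new cycle. They are real and they limit harm after the first cycle. They do not affect the first dose.

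**Conclusion.** The concern holds as stated. On the branch where 130 mg/m2 is rejected, section 5.2 as written gives the listed genotypes the rejected dose, 30% above the general starting dose. On the other two branches the clause is a consistent cap.

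The scope is narrow and probably reflects a drafting gap. The conclusion about the dosing conflict rests on the text alone; only the chance of entering the branch depends on assumed DLT rates. The number of patients affected is unknown, and the primary ORR analysis is unaffected. The point should still be fixed, because a dosing rule that gives the wrong dose when followed literally is a safety matter. A starting dose belongs in the protocol and is not something a statistical analysis plan would supply.

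**What to change.** In section 5.2, replace the fixed genotype dose with a cap: patients with the listed UGT genotypes receive the lower of 130 mg/m2 and the general dose level currently in force. They would then receive 130 when the general dose is 150, 130 when it is 130, and 100 when it is 100. Only the third case changes.

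The cost is one sentence. It needs no extra patients and changes neither the sample size nor the analysis.

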**Number of conversion chemotherapy courses:**

In this study, 8 (no less than 6) courses of conversion chemotherapy are recommended, and some patients also need to appropriately prolong the treatment course. This is mainly because that this study includes patients with unresectable colorectal liver metastases, who usually have a large number of liver metastases, large lesions, with high-risk CRS score. Current clinical practice recommends surgical resection after adequate chemotherapy to achieve more benefit.

**Postoperative adjuvant chemotherapy regimen and the number of courses:**

Patients should receive tumor assessment before postoperative adjuvant chemotherapy, including at least CEA, liver MRI scan + enhanced scan, and chest and lower abdomen pelvic CT (if necessary).

Patients with liver metastases can receive chemotherapy alone with or without cetuximab after surgery. Patients in the cetuximab + mFOLFOXIRI regimen group can receive doublet regimen chemotherapy after surgery. Patients in both groups can receive FUDR HAI on the basis of chemotherapy.

Patients will receive up to a total of 12 courses of chemotherapy before and after surgery, and treatment will be interrupted in the event of disease progression, intolerable adverse reactions, or patient refusal.

**6. Chemotherapy dose adjustment and concomitant medication**

**6.1 Overview**

Toxicities will be assessed according to NCI CTCAE v4.03 criteria starting from the first treatment cycle and will need to be repeated prior to and at the end of each subsequent treatment cycle. The following are general considerations for dose modifications due to chemotherapy-related adverse reactions:

- Dose reductions or interruptions may not be required if, at the discretion of the investigator, the adverse reaction is unlikely to develop into a serious or life-threatening event and will not result in treatment delay or interruption (e.g., alopecia, taste alteration, etc.). If anemia can resolve well with transfusion, no dose reduction or treatment interruption is required.
- If any Grade 1 adverse reactions occur, treatment may be continued at the starting dose without dose interruption.
- Prior to each new treatment cycle, patients should meet the following criteria:

Normal hematologic function (platelets > 90 × 10^9^/L; leukocytes > 3 × 10^9^/L; neutrophils > 1.5 × 10^9^/L).

Serum bilirubin ≤ 1.5 times ULN and transaminases ≤ 5 times ULN.

Serum creatinine < ULN, or calculated creatinine clearance > 50 ml/min (using the Cockcroft-Gault formula).

Recovery to baseline or ≤ Grade 1 from any treatment-related Grade 3/4 non-hematologic adverse reactions (except alopecia).

- If the patient is ineligible for FOLFOXIRI or FOLFOX chemotherapy, treatment with cetuximab or FU/CF chemotherapy can be continued. If the patient is ineligible for cetuximab treatment, FOLFOXIRI or FOLFOX chemotherapy can be continued.

**6.2 Dose modifications due to hematologic toxicity**

Dose modifications during this or subsequent cycles due to DLT are made as follows:

- For Grade 3 ANC decreased, dose modification of investigational drugs (oxaliplatin/irinotecan, 5-FU) is not needed. For Grade 3 PLT decreased, febrile Grade 3 ANC decreased, or Grade 4 ANC decreased, adjust the dose of oxaliplatin/irinotecan to 80% of the original dose. For Grade 4 PLT decreased or febrile Grade 4 ANC decreased, adjust the dose of oxaliplatin/irinotecan to 70% of the original dose.
- After a dose reduction, if the same or higher grade of toxicity recurs, further reduce the dose of oxaliplatin/irinotecan to 60%. If Grade 4 toxicity persists despite dose modification for Grade 4 toxicity, discontinue oxaliplatin/irinotecan and continue the treatment with cetuximab or FU/CF chemotherapy.
- After the second dose reduction, if the same or higher grade of toxicity recurs, discontinue oxaliplatin/irinotecan and continue the treatment with cetuximab or FU/CF chemotherapy.

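### Section 6.2 allows two different actions when Grade 4 neutropenia or thrombocytopenia occurs again after a reduction made for Grade 4, and does not say which one governs

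*Protocol*

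**What the plan says.** The first bullet of section 6.2 sets the first reduction by type and grade of toxicity. One group of events brings this cut: "For Grade 3 PLT decreased, febrile Grade 3 ANC decreased, or Grade 4 ANC decreased, adjust the dose of oxaliplatin/irinotecan to 80" per cent. A second group brings a larger one: "For Grade 4 PLT decreased or febrile Grade 4 ANC decreased, adjust the dose of oxaliplatin/irinotecan to 70% of the original dose". Grade 3 neutropenia without fever calls for no change.

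The second bullet then covers what happens next, in two consecutive sentences. The first is general: "After a dose reduction, if the same or higher grade of toxicity recurs, further reduce the dose of oxaliplatin/irinotecan to 60" per cent. The second concerns Grade 4 only: "If Grade 4 toxicity persists despite dose modification for Grade 4 toxicity, discontinue oxaliplatin/irinotecan and continue the treatment with cetuximab or FU/CF chemotherapy".

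The third bullet covers a later step: "After the second dose reduction, if the same or higher grade of toxicity recurs, discontinue oxaliplatin/irinotecan", again leaving cetuximab or FU/CF.

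Section 6.1 sets the conditions for starting a cycle: "Prior to each new treatment cycle, patients should meet the following criteria". The list includes neutrophils above 1.5 and platelets above 90 × 10^9/L.

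**The concern.** Take a patient whose dose was cut because of Grade 4 neutropenia and who has Grade 4 neutropenia again on the reduced dose. Grade 4 after Grade 4 is the same grade, so the general sentence leads to the 60% step. It is also Grade 4 toxicity seen despite a modification made for Grade 4, so the next sentence can be read as leading to discontinuation. Nothing in the bullet ranks the two sentences or explains why the verb changes.

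This is a safety instruction for patients with repeat severe cytopenia, in an open-label trial run at several centres. If sites read it differently, the treatment delivered within an arm depends partly on who reads the rule. The ambiguity may also arise more often in the FOLFOXIRI arm, because section 1 describes more hematologic toxicity with triplet than with doublet chemotherapy.

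**Working it through.** No sample size, power or error rate enters this point, so the check is a reading of the rules against each Grade 4 path.

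**Inputs**
- First reduction (6.2, first bullet): to 80% for Grade 3 platelets (PLT), febrile Grade 3 neutrophils (ANC) or Grade 4 ANC; to 70% for Grade 4 PLT or febrile Grade 4 ANC.
- Rule A (6.2, second bullet, first sentence): same or higher grade returns after a reduction; go to 60%.
- Rule B (6.2, second bullet, second sentence): Grade 4 persists despite a Grade 4 modification; stop oxaliplatin/irinotecan.
- Rule C (6.2, third bullet): toxicity returns after the second reduction; stop oxaliplatin/irinotecan.
- Counts needed to start a cycle (6.1): ANC > 1.5 and PLT > 90 × 10^9/L.
- Grade 4 limits (Appendix III): ANC < 0.5 and PLT < 25 × 10^9/L.
- Schedule (5.2): oxaliplatin and irinotecan on day 1, repeated every 14 days.

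**Step 1: which rules fire on which path**

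| Path | First event and dose | Next event | Rule A | Rule B | Rule C |
| --- | --- | --- | --- | --- | --- |
| 1 | Grade 4 ANC without fever, to 80% | Grade 4 again | 60% | stop | not reached |
| 2 | Grade 4 PLT or febrile Grade 4 ANC, to 70% | Grade 4 again | 60% | stop | not reached |
| 3 | Grade 3 PLT or febrile Grade 3 ANC, to 80% | Grade 4 | 60% | not triggered: the reduction was not made for Grade 4 | not reached |
| 4 | Already at the second reduction | Toxicity returns | superseded by C | no different action | stop |

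The overlap is confined to paths 1 and 2. Path 3 has one instruction. Path 4 has one outcome, and Rule C adds no conflict of its own.

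**Step 2: do the two verbs separate Rules A and B?**
Both drugs are given on day 1, so a reduced dose is first given on day 1 of a later cycle. If section 6.1 is followed, ANC has by then risen from below 0.5 to above 1.5, and PLT from below 25 to above 90. Grade 4 toxicity cannot simply carry over into the reduced cycle. A Grade 4 count seen afterwards has come back, which fits *recurs*, and has come back despite the modification, which can be read as *persists*. One distinction remains possible: Grade 4 that appears after the reduced dose and then fails to recover could be what *persists* means. Section 6.2 does not say so and gives no duration for it.

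**Step 3: size of the difference for one patient**
Taking the 60% as a share of the original dose, which Rule A does not itself state:
- Irinotecan: 0.60 × 130 = 78 mg/m², or 0.60 × 150 = 90 mg/m², against none.
- Oxaliplatin: 0.60 × 85 = 51 mg/m², against none.

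**Step 4: frequency**
The nearest figure is in section 1: 40% agranulocytosis of Grade 3/4 in one earlier study of cetuximab plus triplet. It pools the two grades and says nothing about Grade 4 occurring again after a Grade 4 reduction. No rate for the affected event can be derived from it.

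**The case against.** The strongest reply is that the bullet reads naturally as a general rule followed by a special case. The second sentence has the narrower trigger. If it overrides the first, every rule has a role: the 60% step serves toxicity that returns after a Grade 3 reduction, the second sentence serves Grade 4 after Grade 4, and the third bullet serves what follows the 60% step. A second reply is that *persists* may mean Grade 4 that does not recover after the reduced dose. That would be a different event from one that returns and then resolves. Section 6.1 fits this reading, since it lets a patient who is ineligible for FOLFOX or FOLFOXIRI continue cetuximab or FU/CF, which is where the second sentence leads.

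Both readings are tenable. A reader might infer from the cycle-start counts that Grade 4 after a modified dose is always a recurrence and that the sentences flatly contradict each other. The documents do not support that. The counts exclude only Grade 4 carried over from before the reduced dose, not Grade 4 that appears afterwards and fails to resolve.

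The replies do not remove the ambiguity, because they disagree with each other. For Grade 4 that returns and then recovers, the special-case reading gives discontinuation and the non-recovery reading gives 60%. The protocol marks an exception openly elsewhere: section 6.5 says that its general principles do not apply to a second Grade 4 non-hematologic event. Section 6.2 has no such signal.

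**Conclusion.** The point holds in a limited form. For Grade 4 neutrophil or platelet toxicity that occurs again after a reduction made for Grade 4, section 6.2 supports two actions, 60% of the dose or discontinuation, and states no precedence. The defect is an undefined pair of terms and an unstated order between two rules.

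Three stronger conclusions are tempting and do not follow:
- A reader might take the problem to cover any Grade 4 toxicity after any reduction. After a reduction made for Grade 3, only the 60% instruction applies.
- A reader might say that identical patients will be treated differently. That is possible, not shown; sites may all settle on one reading.
- A reader might infer an effect on the objective response rate or on dose intensity between arms. Section 1 supports more hematologic toxicity with triplet chemotherapy in direction only, and the share of patients with repeat Grade 4 toxicity is not given.

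No statistical figure in the protocol changes. The conclusion assumes that the cycle-start counts in section 6.1 are followed. The mg/m² figures assume that 60% refers to the original dose.

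**What to change.** Amend the second bullet of section 6.2 so that Grade 4 toxicity occurring again after a Grade 4 reduction leads to one action, and state which of the two sentences takes precedence. If *recurs* and *persists* are meant as different events, define each; if not, use one term. The clinical team decides which action stands; this review takes no view on it.

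The cost is a short wording amendment and a notice to sites. It needs no extra patients, visits or procedures, and does not touch the sample size or the analysis.
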